## Abstract

Supplemental Digital Content is available in the text

## Introduction

1

Cardiovascular disease (CVD) remains the leading cause of death and years of life lost worldwide.^[1]^ In addition, since 1990, there has been a 42% [95% confidence interval (95% CI) 36–48] increase in the absolute number of deaths due to ischemic heart disease globally.^[2]^ In Brazil, CVD has also been the leading cause of mortality since the 1960s and has accounted for a substantial percentage of all hospitalizations. In 2011, CVD was responsible for 31% of all deaths, with ischemic heart disease being the leading cause.^[3]^

Individuals with a prior cardiovascular event have a 5 times greater chance of having another event than people without known CVD.^[4]^ Taking this information into account, a growing body of evidence suggests that adequate management of risk factors substantially reduces unfavorable clinical outcomes, including death, recurrence of ischemic events, and need for revascularization.^[5]^ The World Health Organization estimates that 75% of cardiovascular mortality can be reduced with appropriate changes in lifestyle.^[6]^ When lifestyle interventions are applied to individuals with coronary or other atherosclerotic vascular disease, it is considered secondary prevention.^[7]^

There is a diversified effort to translate cardiovascular science into guidelines to assist health professionals in the management of CVD, for conditions such as acute coronary syndrome (ACS) and its secondary prevention. Despite the increased use of proven effective therapies, adherence to the available recommendations is still below ideal.^[8–10]^ Several telehealth tools, such as text message services—short message service (SMS), can be simple and inexpensive alternatives to encourage healthy life habits and optimize medication adherence.^[11]^

Studies that used SMS as an intervention have shown beneficial results in risk factors control for ischemic heart disease in outpatient settings. Martin et al^[12]^ showed a significant short-term increase in the levels of physical activity of cardiac outpatients. Glynn et al^[13]^ demonstrated similar results on patients seen in rural primary care in an Irish municipality and Wald et al^[14]^ showed an improvement on medication adherence in patients taking blood pressure and lipid-lowering therapies for CVD prevention. Corroborating these findings, using an SMS application, Chow et al^[11]^ found modest improvements in cholesterol levels and moderate reductions on blood pressure, body mass index (BMI), and smoking in patients with coronary artery disease.

Despite the promising results, there is insufficient evidence to draw definite conclusions about the effectiveness of SMS interventions for secondary prevention of CVD, particularly in low- and middle-income countries, where mobile health strategies can have a great impact lowering the costs of health care. Although the access to mobile phone is high in countries such as Brazil, with a density of 112.87 phones/100 inhabitants,^[15]^ the understanding of the messages sent by SMS may not be the same as in high-income countries due to the lower educational stratum of the population.

The IMPACS study will be a 2-arm, parallel, double-blind, and randomized clinical trial. The main purpose of this study is to evaluate whether, in patients who are in secondary prevention of CVD, the use of SMS improves control of CVD risk factors during the 6-month follow-up after discharge by ACS, when compared with the usual treatment. The secondary aim is to develop a wide SMS message bank, semi-personalized, which will include information about lifestyle modifications, medication adherence, and CVD risk factor control. This study, as a randomized clinical trial protocol, followed the recommendations of the Standard Protocol Items (SPIRIT).

## Methods

2

### Participants (study setting and eligibility)

2.1

The study population will include patients of the University Hospital of Universidade Federal de Minas Gerais (UFMG's University Hospital), a public and general hospital in southeast Brazil, who were admitted due to diagnosis of ACS. Patients will be also participants of the “Good Practice Program in Cardiology,”^[16]^ a program of the Brazilian Cardiology Society, Ministry of Health (Brazil), and American Heart Association (United States of America).

Inclusion criteria are as follows:

(1)Consecutive patients admitted at the UFMG's University Hospital with primary or secondary diagnosis of ACS and discharged for outpatient follow-up. Confirmed diagnosis of ACS will be defined based on The Third Universal Definition of Myocardial Ischemia.^[17]^(2)Age ≥18 years, of both sexes;(3)Patients who are able to receive SMS in their own mobile phone.

Exclusion criteria are as follows:

(1)Refusal or inability to sign the informed consent;(2)Complete illiteracy.

### Interventions

2.2

The usual care group (IMPACS control group) will receive standard discharge treatment and standard hospital follow-up. They will monthly receive text messages thanking for their participation in the trial and reminders of trial appointment.

The intervention group (IMPACS intervention group) will receive the usual post-discharge care for ACS, instructions and information, as well as the SMS intervention program. The SMS program will include a variety of topics, such as standard follow-up care reminders and general self-management and healthy habits texts to inform and engage patients in care. The Intervention will run for 6 months and the program will consist of 4 modules, according to baseline characteristics of participants:

(1)Module 1: nonsmokers and free of diabetes;(2)Module 2: nonsmokers and diabetic patients;(3)Module 3: smokers and nondiabetic patients;(4)Module 4: smokers and diabetic patients.

Modules 2 and 4 are subdivided into 2 according to whether or not diabetic patients are in use of insulin. Texts will be sent out 4 times per week for 180 days at pre-established times, with the first SMS being sent immediately after hospital discharge. All participants included in the same module will receive the same texts and in the same order, regardless of the allocation time in the study. No cross-over between groups is expected.

All participants will also be followed by the UFMG's University Hospital Coronary Artery Disease outpatient clinic and rehabilitation program, unless they choose otherwise. IMPACS researchers will be independent of attending physicians and will not interfere with patient care.

#### Technological development

2.2.1

Dedicated software was developed by The Telehealth Center of UFMG's University Hospital to send 1-way SMS between server (Windows) and participant's mobile phone.^[18]^ The software has a bank of text messages that allows identification and scheduling for submission of SMS on predetermined dates. To test the software developed and the initial acceptability of text messages sent, a pilot study was conducted and it is described in Appendix 1.

#### Text messages

2.2.2

The messages that will be used in this study were developed by the research group, offering advice, motivation and information about medication adherence, increase of regular physical activity, adoption of healthy dietary habits, and smoking cessation (if appropriate). The content of the messages is based on the Brazilian Society of Cardiology Guidelines, available online.^[19]^ Messages will be semi-personalized because the objective is to combine general information with personalized content, using information provided in baseline questionnaires. The bank of text messages, after being developed, was reviewed by individuals not involved in the study to check for language issues and evaluation of understanding. The main goal was to make messages easy to read and understand, for all cultural and social levels. Text messages content according to each module is summarized in Table 1 and examples of text messages sent to the IMPACS intervention group can be seen in Table 2.

**Table 1 T1:**
[figure not shown]
Text messages according to modules based on characteristics of participants.

**Table 2 T2:**
[figure not shown]
Examples of text messages sent to the IMPACS intervention group.

At study entry, all participants will be given brief training (three to five minutes) of how to read text messages, save, and delete them, if necessary. The Telehealth Center of UFMG's University Hospital will manage the SMS through a computerized messaging engine, and because of that, participants will be instructed not to respond to them. Interactive communication will only occur via e-mail, if the patient shows an intention to discontinue his/her participation in the study. Messages will be sent at no cost to the participants.

### Outcomes

2.3

Participants will have outcomes measured at 6 months (±1 month) after hospital discharge, in the follow-up appointment pre-scheduled by the study's researchers. Researchers blinded to treatment allocation will collect the data.

(1)Primary endpoint: The primary outcome is achieving 4 or 5 points in a risk factor control score, which combine the cluster effect of 5 main modifiable risk factors for ACS [low-density lipoprotein cholesterol - LDL-C <70 mg/dL, blood pressure <140/90 mm Hg, regular exercise (≥5 days/week × 30 minutes of moderate exercise per session), nonsmoker status, and BMI <25 kg/m^2^].(2)Secondary endpoints: Plasma LDL-C levels, objective level of physical activity, blood pressure, medication adherence, proportion of nonsmokers, BMI, death from any cause, rehospitalization, and cardiovascular death.

### Sample size

2.4

A sample size of 141 patients was estimated, increasing to 160 to allow for a 15% loss to follow-up, 2-tailed and at a 5% significance level, would have 80% power to detect a difference of at least 19% between the intervention and the control groups in achieving 4 or more of the 5 modifiable risk factors listed above (Risk Factor Control Score), based on the findings of the study by Chow et al.^[11]^ An interim analysis before the end of the patient allocation will be done to evaluate the follow-up losses with the objective of reassessing the sample size initially considered.

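### The three sample-size figures in section 2.4 do not agree: 160 randomised with 15% loss leaves 136 evaluable patients, not 141

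*Protocol article*

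**What the plan says.** Protocol article, section 2.4 (Sample size), gives the evaluable number and its inflation together: "A sample size of 141 patients was estimated, increasing to 160 to allow for a 15% loss to follow-up". The test is "2-tailed and at a 5% significance level", and the sample "would have 80% power to detect a difference of at least 19" percentage points in the proportion reaching 4 or more of the 5 risk-factor targets. The control rate is not stated; the assumption is described only as "based on the findings of the study" of an earlier text-message trial. The section then plans an interim review of follow-up losses, before allocation ends, to reconsider the sample size.

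Section 2.5 (Allocation and blinding) sets 1:1 allocation in blocks of 4. Section 2.8 (Statistical methods) names the chi-square test for the primary outcome. No other section gives a different sample size or loss rate.

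**The concern.** An allowance for loss should return the evaluable number once the loss has occurred. Here it does not: applying 15% loss to 160 gives a number below 141. One of the three figures is therefore wrong as written, and a reader cannot tell which.

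Two things depend on it. The first is the link between the recruitment target and the stated power at the planned loss rate. The second is the interim review. Its purpose is to judge whether 160 is still adequate given the observed losses, and 15% is the only loss benchmark in the document. If 141 is the true requirement and observed loss lies between about 12% and 15%, a team relying on the stated allowance would judge 160 sufficient although fewer than 141 evaluable patients would remain.

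**Working it through.** **Inputs.** From section 2.4: evaluable N = 141, randomised N = 160, loss d = 15%, two-sided alpha = 0.05, power 80%, difference 0.19 (read as absolute). From section 2.5: 1:1 allocation, blocks of 4. From section 2.8: chi-square test. Not stated: control rate and sample-size formula.

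**Step 1. Try to reproduce 160.**
- Standard inflation, N/(1 − d): 141/0.85 = 165.9, so 166 (168 in whole blocks of 4).
- Common shortcut, N × (1 + d): 141 × 1.15 = 162.15, so 163 (164 in blocks of 4).

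Neither gives 160. The shortcut comes closest, and 160 may be a rounding of it, but the document does not say so.

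**Step 2. Work back from 160.**
- Evaluable after 15% loss: 160 × 0.85 = 136, which is 5 fewer than 141.
- Largest loss at which 141 remain: 1 − 141/160 = 11.9%.
- 136/0.85 = 160 exactly, so 160 and 15% agree with each other if the requirement was 136.

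**Step 3. Power at 136, if 141 gives exactly 80%.** The standardised effect scales with the square root of N, so to a good approximation no control rate is needed:

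Power = Φ[(1.960 + 0.842) × √(136/141) − 1.960] = Φ[2.802 × 0.982 − 1.960] = Φ(0.791) = 78.6%.

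As a cross-check, solving the pooled two-proportion formula for a total of 141 gives 11.3% v 30.3%. With 68 per arm, power is then 78.5% and the difference detectable with 80% power is 19.4 points.

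**Step 4. Range over the unstated control rate (assumption).** The table gives power for a 19-point difference with 136 evaluable patients (68 per arm), from the pooled formula without continuity correction.

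| Control v intervention | Formula under which N is near the stated figures | Power at 136 |
|---|---|---|
| 7% v 26% | continuity-corrected, N = 138 | 85.5% |
| 7.5% v 26.5% | continuity-corrected, N about 141 | 84.7% |
| 10% v 29% | pooled, N = 136 | 80.5% |
| 11% v 30% | pooled, N = 140 | 79.0% |
| 12% v 31% | unpooled, N = 140 | 77.6% |
| 13% v 32% | unpooled, N = 144 | 76.2% |

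The mirror-image rates (for example 70% v 89%) give the same results. So 141 can be neither confirmed nor refuted from the document, and power at 136 lies on either side of 80% depending on how 141 was obtained.

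**The case against.** A reader might infer that the trial fails to deliver its stated 80% power, or that 166 patients must be randomised. The documents support neither.

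- **Power.** With no control rate or formula, power at 136 is not known. If 141 came from a continuity-corrected formula (control rate about 7.5%), 136 patients analysed with an uncorrected chi-square test would have about 84.7%. This stands: 78.6% holds only on the premise that 141 gives exactly 80%.
- **Which figure is wrong.** Since 136/0.85 = 160, the inflation may be right and 141 misstated; 10% v 29% gives exactly 136 under the pooled formula. Alternatively, 15% may be the loose figure. This also stands, and it means the remedy cannot presume that 160 is the error.
- **Planned reassessment.** Section 2.4 treats the sample size as an initial figure, to be reconsidered on follow-up losses before allocation ends, so a shortfall need not persist. This stands in part. The review could repair the shortfall, but it does not make the sentence correct, and the only loss benchmark available to it is the 15% in question.
- **Materiality.** On the conditional reading the loss is about 1.4 points of power and 0.4 points of detectable difference, less than the uncertainty from the unstated control rate. This stands, and argues for a correction of the text rather than a change of design.

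None of this reconciles 141, 15% and 160. Nor is it a matter of detail left out by a condensed article: the published figures contradict one another.

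**Conclusion.** Wrong as written, with a small consequence. The inconsistency follows from arithmetic alone and needs no assumption: the stated allowance leaves the evaluable number 5 short, or equivalently the randomised number 6 short.

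The effect on power is conditional. Taking 141 as the number that gives exactly 80%, power at 15% loss is about 78.6% and the detectable difference about 19.4 points instead of 19. Over the control rates and formulas that bring the calculation near the stated figures, power at 136 runs from about 76% to 85.5%. This is a planning and reporting inconsistency, not evidence of a seriously underpowered trial.

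**What to change.** Check the original calculation, then restate the sentence in section 2.4. The recruitment target of 160 can stay.

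- **If 141 is right:** state that 160 allows for about 12% loss, and that at 15% loss 136 remain, with about 78.6% power for 19 points on the premise that 141 gives 80%. That power should not be given as an unconditional figure. If the sponsor would rather keep 141, 15% and 80% together, the matching total is 166 (168 in blocks of 4).
- **If the requirement was 136:** replace 141 with 136; 160 and 15% then stand.
- **In either case:** state the control rate and the formula used, so that the evaluable number can be reproduced.
- **Interim review of follow-up losses:** use the corrected threshold, about 12% if 141 stands and 15% if the requirement was 136.

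The cost is an edit of a sentence or two and, if 141 stands, a slightly less favourable power statement. No extra patients are needed unless the sponsor chooses to keep 141 evaluable at 15% loss.

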### Allocation and blinding

2.5

After obtaining written informed consent, the data of each patient will be entered into an online database. To reduce predictability of a random sequence, a blocking randomization will be provided in blocks of 4 patients following the date of patient enrollment. The computerized randomization program is only accessible to administrators of the Telehealth Center of the UFMG's University Hospital. The random allocation sequence will follow a uniform 1:1 ratio and the researchers, data collectors, and attending physicians will be blind to the treatment allocation (double blinding).

### Data collection methods

2.6

The eligible patients will be identified by daily assessment in the Coronary Intensive Care Unit of UFMG's University Hospital and followed up throughout the hospitalization for data collection. All data collectors will undergo specific training for understanding and systematically applying the study protocol.

Demographic, educational, socioeconomic, and clinical characteristics of the study participants will be collected at baseline. At this stage, ACS type and severity criteria, diagnostic and therapeutic procedures performed in the in-hospital phase, and prescribed medications at hospital discharge will also be collected. Before hospital discharge (up to 48 hours before discharge), patient weight, height, heart rate, and blood pressure will be additionally measured for future analysis.

The participant timeline is described in Appendix 02 and the flow chart of study design in Table 3.

**Table 3 T3:**
[figure not shown]
Flow chart of study design.

The data collection protocols are briefly summarized in the following:

(1)Plasma LDL-C level: measured at baseline and 6 months after hospital discharge (before the outpatient appointment), after 12 hours of fasting, in the same laboratory. Measurement of total cholesterol, triglycerides, and high-density lipoprotein cholesterol will be done with CHOL VITROS Chemistry Products slides from Ortho Clinical Diagnostics (VITROS 5.1 and VITROS 5.600/colorimetric method). For LDL-C dosage, the value is generally calculated. When triglycerides value >400 mg/dL, we will perform direct dosing of LDL-C using the reagent LDL VITROS Chemistry Products from Ortho Clinical Diagnostics (VITROS 5.1 and VITROS 5.600 / End point Method).(2)Level of physical activity: measured by the International Physical Activity Questionnaire Short Form (IPAQ-SF) ^[20]^ at baseline and 6 months after hospital discharge. The measure will be validated in one-fifth of the participants by using accelerometers (Actigraph wGT3X-BT; Pensacola, FL). A question about whether the patient is performing scheduled physical activity following the recommendation of the Brazilian Society of Cardiology will also be included in the follow-up questionnaire.^[21]^(3)Blood pressure: measured at baseline and 6 months after hospital discharge by the same automatic blood pressure device (OMRON model HEM-705 CP Intellisense) and OMRON blood pressure cuffs up to 48 hours before hospital discharge and in the follow-up visits. Three resting measurements will be made, with the patient in the seated position, with the arm supported. The mean of the last 2 readings will be considered for data analysis.(4)Medication adherence: measured at 6 months after hospital discharge via “Medida de Adesão aos Tratamentos” – MAT,^[22]^ a validated instrument composed of 6 items that evaluate the behavior of the individual in relation to daily use of medicines. The answers are obtained by means of a 6-point ordinal scale that varies from “always” [1] to “never” [6]. The values obtained with the answers to the 6 items are summed and divided by the number of items (values vary from 1 to 6). Subsequently, values 5 and 6 are computed as 1 (adherent) and the others are computed as 0 (nonadherent).(5)Proportion of nonsmokers: measured at 6 months after hospital discharge by self-report. The participant will answer the following question: “Are you smoking after hospitalization?”, for which he/she could answer “Yes” or “No.” The answer will be also confirmed by a Carbon Monoxide Meter Breath Test (piCO Smokelyzer, Kent, UK). This is an indirect and noninvasive measure of blood carboxyhemoglobin. The device directly measures carbon monoxide (ppm) and carboxyhemoglobin is a calculation based on clinical evidence. The values obtained by the device are 0 to 6 (nonsmoker range), 7 to 19 (light smoking range), and 20 or more (heavy smoking range).^[23,24]^(6)BMI: measured at baseline and 6 months after hospital discharge. BMI will be calculated by weight measured in kilograms divided by height in square meters.(7)Rehospitalization: measured at 6 months by means of self-report and medical discharge records.(8)Cardiovascular death and death from any cause: measured at 6 months by report of relatives and confirmed by death certificate or medical records.(9)Health literacy questionnaire: measured at baseline. A version consisting of 18 items of The Short Assessment of Health Literacy for Portuguese speaking Adults (SAHLPA-18) ^[25]^ will be applied to participants at the baseline.(10)Follow-up questionnaire: a follow-up questionnaire with self-report of reading messages will be applied as well as questions about acceptability and understanding (Appendix 3).

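### The medication-adherence cut-off names only the whole values 5 and 6 of a six-item mean, so read literally it is non-monotone, and the sensible readings disagree

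*Protocol article*

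**What the plan says.** Protocol article, section 2.6 (Data collection methods), item (4), measures medication adherence at 6 months with the MAT, described as "a validated instrument composed of 6 items that evaluate the behavior of the individual in relation to daily use of medicines". On the answers it says: "The answers are obtained by means of a 6-point ordinal scale that varies from “always” [1] to “never” [6". On the score: "The values obtained with the answers to the 6 items are summed and divided by the number of items (values vary from 1 to 6". On the final coding: "Subsequently, values 5 and 6 are computed as 1 (adherent) and the others are computed as 0 (nonadherent".

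Section 2.3 (Outcomes) names adherence among the secondary endpoints: "Secondary endpoints: Plasma LDL-C levels, objective level of physical activity, blood pressure, medication adherence, proportion of nonsmokers". It is not one of the five factors in the primary risk factor score.

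No other part of the article gives a rounding step or a lower limit for the adherent category.

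**The concern.** The score is an average and will usually be a fraction, but the coding rule speaks only of two whole values and sends everything else to nonadherent. The coding comes after the averaging, so it applies to the mean and not to single answers.

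Followed to the letter, the rule does not increase with adherence. A patient whose mean rises from 5.00 to 5.50 would move from adherent to nonadherent. If the letter is set aside, the analyst must choose a cut-off that the article does not fix, and that choice could be made after the data are seen. Medication adherence is a named secondary endpoint and one of the main topics of the messages, so its definition should leave no such choice.

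**Working it through.** **Inputs (section 2.6, item 4).** Six items; each answer is a whole number from 1 to 6; score = sum / 6. High scores count as better adherence, because the top values are the ones coded adherent.

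**Step 1: the stated range.** The sum runs from 6 × 1 = 6 to 6 × 6 = 36, so the mean runs from 6/6 = 1 to 36/6 = 6. This reproduces the article's range of 1 to 6.

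**Step 2: attainable values.** The sums 6 to 36 give 36 − 6 + 1 = 31 possible means, spaced 1/6 apart.

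**Step 3: three readings of the rule.**

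| Sum | Mean | Literal (exactly 5 or 6) | Mean ≥ 5 | Rounded to 5 or 6 (mean ≥ 4.5) |
|---|---|---|---|---|
| 27 | 4.50 | 0 | 0 | 1 |
| 28 | 4.67 | 0 | 0 | 1 |
| 29 | 4.83 | 0 | 0 | 1 |
| 30 | 5.00 | 1 | 1 | 1 |
| 31 | 5.17 | 0 | 1 | 1 |
| 32 | 5.33 | 0 | 1 | 1 |
| 33 | 5.50 | 0 | 1 | 1 |
| 34 | 5.67 | 0 | 1 | 1 |
| 35 | 5.83 | 0 | 1 | 1 |
| 36 | 6.00 | 1 | 1 | 1 |

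The literal column goes 1, 0, 0, 0, 0, 0, 1 from a mean of 5 upward, so it is non-monotone. The other two columns are monotone but differ for sums 27 to 29. The rounded column takes halves upward, which is itself a convention that would have to be stated.

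**Step 4: illustrations of size.** The article gives no distribution of answers, so these rest on assumptions, including independence between items.

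- *Literal rule, patients who answer only 5 or 6.* If each item is 6 with probability p, the share coded nonadherent is 1 − p⁶ − (1 − p)⁶.
  - p = 0.5: 1 − 0.0156 − 0.0156 = 0.969
  - p = 0.7: 1 − 0.1176 − 0.0007 = 0.882
  - p = 0.9: 1 − 0.5314 − 0.000001 = 0.469
- *Gap between the two sensible readings.* Assume 55% of answers are 6, 30% are 5, 10% are 4 and 5% are lower. The distribution of the sum is the six-fold convolution of this item distribution. P(27 ≤ sum ≤ 29) is 0.105 if the lowest 5% all sit at 3, and 0.171 if they all sit at 1. In the same two cases, P(mean ≥ 5) is 0.886 and 0.770, and the literal rule codes 0.127 and 0.111 adherent.

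**The case against.** The strongest reply is that nobody would run the literal rule. The article says that it only summarises its data collection protocols briefly, and naming the values 5 and 6 is natural shorthand for the top band of a 1-to-6 scale. It also cites a validated instrument, whose source would give the cut-off for fractional means, and a condensed article may leave such detail to that source, to the full protocol or to the SAP.

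Much of this stands. The literal coding is probably not intended, and the document gives no sign that it will be applied. A reader might infer that most well-adherent patients will be misclassified; the article does not support that. It would require the least plausible reading to be carried into the analysis, together with item distributions that the article does not supply. Items of one scale are likely to be correlated, which would probably put more patients at exactly 6.00 and shrink the literal rule's error. The percentages above are therefore illustrations, not estimates.

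Two things survive. First, this is not a detail left out: the article states a rule, and that rule taken as written gives a wrong ordering. Second, the charitable reading does not settle the matter, because shorthand for the top band fits both a mean of at least 5 and a mean that rounds to 5 or 6. For the same reason, a cut-off of at least 5 cannot simply be presumed to be what the authors meant.

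**Conclusion.** The concern holds as a defect in the stated definition. Literally, five of the seven attainable means from 5 to 6 are coded nonadherent while 5.00 is coded adherent. That result is pure arithmetic and needs no assumption. On the sensible readings the cut-off remains unfixed for means of 4.50, 4.67 and 4.83, which is about 10% to 17% of patients under the assumed independent item distribution.

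Severity is minor to moderate. Adherence is one of nine secondary endpoints in section 2.3. It does not enter the primary risk factor score or the sample size in section 2.4, and the primary comparison in section 2.8 is untouched. It would be wrong to infer that the trial's main conclusion is at risk. If the analysis already uses a monotone threshold fixed in advance, only the wording needs correcting. The instrument's own scoring source was not available, so which threshold is right is left open here.

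**What to change.** Before unblinded analysis, replace the dichotomisation sentence in section 2.6, item (4), with one monotone rule on the mean. Either of these forms would do:

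- a mean of 5 or more is coded 1 (adherent), and a mean below 5 is coded 0; or
- the mean is rounded to the nearest integer, with the handling of halves stated, and a rounded value of 5 or 6 is coded 1, any other 0.

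The choice should be confirmed against the validated scoring of the instrument, and the same rule used in the analysis code. Reporting the mean score by arm alongside the dichotomy is optional.

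The cost is one sentence and a check of the instrument's source. No new data are needed, because the rule is applied to the six answers that the score already requires.
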